**Abstract:**

Gastroparesis (GP), defined as delayed gastric emptying without any mechanical obstruction affects up to 10 million individuals in the United States. Improvement of symptoms is achieved in up to 50-60% of drug refractory patients treated with gastric electrical stimulation (GES), but this therapy has minimal or no effect on the acceleration of gastric emptying (GE). To address this therapeutic deficiency, we have added surgical pyloroplasty (PP) as a supplementary procedure to accelerate GE in drug refractory gastroparetics undergoing implantation of GES. Based on our experience, there was more than 70% improvement in total GP symptom scores (TSS) in the follow-up evaluation and GE was normalized in 60 % of GP patients who received combined GES and pyloroplasty, suggesting that the combination of PP and GES significantly accelerate gastric emptying and improve GP symptoms exceeding the results previously achieved by GES alone. Now, the question is whether pyloroplasty alone could be sufficient for the achievement of both subjective and objective goals of improvement in drug refractory gastroparesis. Therefore, in the current proposal, we plan to compare TSS outcome, quality of life and GE in drug refractory GP patients who will receive both GES implantation and PP during the surgery and then are evaluated during a GES-off or –On period based on a randomized double blind study design. As a secondary goal, we will also examine whether the baseline pyloric and antral interstitial cells of Cajal (ICC) counts as well as the presence of pyloric fibrosis could predict clinical response to PP.

42  
43  
44  
45 **Research Plan: A) Specific Aims**

46 **1)** To assess the effects of gastric electrical stimulation (GES) and pyloroplasty on total GP  
47 symptoms scores (TSS) and quality of life in drug refractory gastroparetic patients during GES -  
48 ON and GES -OFF periods.

49 **2)** To assess the effects of gastric electrical stimulation (GES) and pyloroplasty on gastric  
50 emptying of a radiolabeled marker in drug refractory gastroparetic patients during GES-ON and  
51 GES -OFF periods.

52 **3)** To understand whether pyloroplasty alone is effective for achieving both subjective and  
53 objective goals of improvement in drug refractory gastroparesis.

54 **4)** To understand whether the status of antral and pyloric ICC counts and/or the presence of  
55 pyloric fibrosis predicts the clinical outcome.

56  
57 **B) Background/significance:**  
58

59 Gastroparesis (GP), affecting up to 10 million individuals in the United States, is a relatively  
60 common gastrointestinal (GI) motility disorder and is defined as delayed gastric emptying without  
61 any mechanical obstruction. Gastroparesis presents with upper GI symptoms such as nausea,  
62 vomiting, bloating, postprandial fullness, early satiety and abdominal pain. The etiology of  
63 gastroparesis is not well recognized and the majority of cases are idiopathic (ID-GP), while many  
64 others are diabetic (DM-GP). Patients with gastroparesis suffer from nutritional deficiencies and  
65 metabolic consequences as well as impaired social activities and quality of life. Treatment of  
66 gastroparesis is based on alleviating symptoms, correcting nutritional abnormalities and targeting  
67 the underlying causes, although it is usually challenging and often disappointing . Therefore,  
68 studying the treatment options of this debilitating disorder are among the priorities in the field of GI  
69 motility disorders.

70  
71  
72 Clinically gastroparesis is categorized as mild, moderate and severe. Mild gastroparesis presents  
73 with occasional symptoms which do not have a significant impact on work and family functioning.  
74 The treatment in this group is based on diet modification, antiemetics and glucose control.  
75 Moderate gastroparesis presents with daily but not continuous symptoms and occasional  
76 hospitalization, interfering with work and family functioning. Diet modifications, prokinetics, one or  
77 more antiemetics and glucose control as well as addressing pain and psychological aspects are

recommended in these patients. In severe Gastroparesis daily continuous symptoms are present resulting in multiple hospitalizations and inability to work and function. Severe gastroparesis is treated with combining prokinetics, multiple antiemetics and nutrition enteral support. Up to 30% of gastroparetic patients fail current medical therapy and need surgery including gastric electrical stimulation (GES) implantation and/or pyloroplasty as the next step.

GES is indicated for the treatment of chronic, intractable nausea and vomiting secondary to diabetic or idiopathic gastroparesis since 2000 under a Humanitarian Device Exemption (HDE) and involves implantation of a pulse generator in the abdominal wall and 2 electrodes into the muscularis propria of the stomach. Based on our experience as well as other national centers, the improvement of symptoms is variable with the maximal response up to 50-60%, but this therapy has minimal or no effect on the acceleration of gastric emptying (GE).

Pyloric dysfunction is recognized as a significant component of gastroparesis. Pylorospasm has been hypothesized to be present in both diabetic GP and ID-GP based on pyloric dysfunction identified by pyloric motility findings. In addition, the lack of acceleration of the delayed GE by GES raises the question as how much better the outcome would be if gastric emptying could be accelerated. This is the rationale for the addition of a surgical pyloroplasty performed at the time when GES is implanted. Surgical papers have suggested that pyloroplasty alone could have a role in patients with GP. Our recent study on pyloroplasty combined with GES showed that GE was normalized in 60% of patients with GP. Patients who received only GES therapy decreased their TSS severity score by <50%, while those patients receiving pyloroplasty and GES had improvement in the severity of gastroparetic symptoms by >70%.

**Despite these findings, the question could be asked whether pyloroplasty alone without GES could generate similar results to GES plus pyloroplasty.** To answer this question, a double-blind and randomized study should be performed on GP patients who receive combined GES implantation and pyloroplasty. Severity and frequency of gastroparesis symptoms, quality of life, hospitalization, changes in antiemetic/prokinetic and analgesic medications and glucose control parameters in diabetes (HbA1c) will be assessed during: (a) a baseline pre-op period, (b) on a day of surgery, (c) 3 months GES-ON and -OFF periods and (d) last follow up visit. Gastric emptying with a radiolabeled meal will performed as a standard of care test, the way it is

conducted now on all patients receiving GES.

Additionally, as reported, approximately 40% of GP patients who are refractory to medical therapy and requiring GES therapy have a depletion of antral ICC. Moreover, our recent research has revealed that more than 70% of these patients show depletion of pyloric ICC. Therefore, we would like to assess whether pyloric and antral ICC counts could predict response to pyloroplasty during GES-ON and -OFF periods .

This concept of our study requires patients to sign, the specific IRB-approved consent form for E14018 study in order to provide a tissue sample as it is described under that protocol.

## C) Preliminary data

### C1) GES-ON plus Pyloroplasty:

A pilot study [abstract submitted to DDW 2016] was designed to assess the long term efficacy (follow-up visits: 3 to 38 months) and safety of combined GES implantation and PP in GP patients who were referred to our clinic from September 2012 to June 2015. Twenty-seven [23 females; mean age 43 years old (23–63); mean weight 148 lbs (86–245)] drug-refractory GP patients who underwent surgical implantation of the GES together with the Heineke-Mikulicz PP during the study period were included. There were 17 diabetics (DM) and 10 idiopathics (IP). There was ~71% improvement in TSS in the follow-up evaluation (Table 1). After surgery, the mean retention of the radiolabeled meal decreased by 29.6% and 48.7% at 2 and 4-hrs, respectively and GE was normalized in 60 % of GP patients. There were no post-surgical complications or technical problems related to combining PP with GES.

**Table 1) The severity of upper gastrointestinal symptoms in gastroparetic patients at baseline and after surgery (gastric electrical stimulator implantation plus pyloroplasty).**

|          | Nausea       | Vomiting     | Early Satiety | Bloating    | Post-Prandial Fullness | Epigastric Pain | Epigastric Burning |
|----------|--------------|--------------|---------------|-------------|------------------------|-----------------|--------------------|
| Pre-Op*  | 3.6 (0.4)    | 3.2 (1.2)    | 3.2 (0.7)     | 2.5 (1.3)   | 2.8 (0.9)              | 2.7 (1.4)       | 2.0 (1.8)          |
| Post-Op* | 1.1 (1.1)*** | 0.6 (1.0)*** | 0.9 (1.0)***  | 0.9 (1.2)** | 1.0 (1.1)***           | 1.0 (1.5)***    | 0.9 (1.5) †        |

\* data represents mean (standard deviation), \*\*P<0.01, \*\*\*P<0.001, †n's. not significant

## C2) GES-ON without pyloroplasty:

Gastroparesis patients (n=221; 142 diabetic, 48 idiopathic, and 31 postsurgical) treated with Enterra for 1-11 years were retrospectively assessed; 188 had follow-up visits and data were collected for at least 1 year. TSS, hospitalization days, and use of medications were significantly reduced among all patients. More patients with diabetic (58%) and postsurgical gastroparesis (53%) had a greater than 50% reduction in TSS than those with idiopathic disease (48%). Weight significantly increased among all groups, and 89% of J-tubes could be removed. At end of the follow-up period, all etiological groups had similar, abnormal delays in mean gastric retention. Thirteen patients (7%) had their devices removed because of infection at the pulse generator site. There was ~48% improvement in TSS in the follow-up evaluation, while mean follow-up GE was not significantly different compared to the baseline indicating that GES alone does not significantly accelerate gastric emptying (Table 2).

Table 2) Comparison of Individual Symptom Scores (Mean  $\pm$  SD) Between Baseline and Follow-Up (gastric electrical stimulator implantation only)

|            | Nausea           | Vomiting         | Early Satiety    | Bloating         | Post-Prandial Fullness | Epigastric Pain  | Epigastric Burning |
|------------|------------------|------------------|------------------|------------------|------------------------|------------------|--------------------|
| Pre-Op19.6 | 3.5 (1.6)        | 3 (1.2)          | 2.9 (1.1)        | 2.8 (1.2)        | 2.8 (1.1)              | 2.5 (1.3)        | 2.1 (1.4)          |
| Post-Op    | 1.6 (1.3)
*** | 1.4 (1.3)
*** | 1.5 (1.3)
*** | 1.4 (1.3)
*** | 1.4 (1.2)
***       | 1.3 (1.3)
*** | 0.8 (1.1)
***   |

\* data represents mean (standard deviation), \*\*\*P<0.001

## D) Research Plan

**D1) Patients:** the criteria for patient's selection will be based on a goal to achieve an adequate number of patients from 2 major etiological subgroups of GP (diabetics and idiopathic) among all potential GES candidates. Adult patients (18-70 years old) will be approached regarding this research trial.

### Inclusion criteria:

Documented diagnosis of GP for > 1 year and refractoriness to anti-emetics and prokinetics; more than 7 emetic episodes per week; and delayed GE (gastric retention greater than 60% at 2 h and/or greater than 10% at 4 h) based on a 4-h standardized radionuclide solid meal test.

### Exclusion Criteria:

Organic or pseudo-obstruction, primary eating or swallowing disorders, positive pregnancy test result, psychogenic vomiting, peritoneal dialysis, drug dependent, morbid obesity, active malignancy and whoever received PP or GES in the past.

**D2) Sample Size:** As this study is designed to conclude that pyloroplasty is not inferior to GES plus pyloroplasty, the sample size for the non-inferiority trial by including % normalization of the GE as the binary outcome is calculated based on: "Blackwelder WC."Proving the Null Hypothesis" in Clinical Trials. Control. Clin. Trials 1982; 3:345-353." GE was normalized in 60 % of GP patients with GES-ON

plus Pyloroplasty based on our preliminary data. On the other hand, based on our patients' database, GES alone normalizes GE in around 18% of GP patients, predominantly in idiopathic GP. By defining non-inferiority limit equal to  $(60 - 18 = 42\%)$ , and percentage of success in the GES-ON plus pyloroplasty group, 17 patients will be included in each arm of this study. Therefore, this study is designed to include overall 34 drug-refractory GP patients who will undergo surgery for GES implantation plus pyloroplasty. Based on our records, we have at least 2 surgeries per month; therefore, we predict that it takes approximately 1.5 years to recruit all patients.

**D3) Study Design:** After receiving IRB approval, the patients will be screened and the project will be discussed with the potential candidates for GES implantation plus pyloroplasty. Based on the inclusion/exclusion criteria, the baseline gastric emptying test (GET) based on the 4-h standardized radionuclide solid meal protocol will be performed and 34 patients will be included in the study. Our effort would be to include similar numbers of idiopathic and diabetic patients in each intervention group based on a block randomization method. The patients will be followed up for 1 month, while their PAGI-SYM, PAGI-QOL and TSS severity/frequency will be recorded on a Standardized Symptoms Interview Form, which assesses the symptoms of gastroparesis occurring during the last 2 weeks before the interview for severity of vomiting, nausea, early satiety, bloating, postprandial fullness, and epigastric pain. The severity of each symptom will be graded by the patients as 0=absent, 1=mild (not influencing usual activities), 2=moderate (diverting from, but not urging modifications, of usual activities), 3=severe (influencing usual activities, severely enough to urge modifications), and 4=extremely severe (requiring bedrest). The sum of the severity ratings of the six symptom subscores comprises the overall total symptom score (TSS) in severity.

PAGI-SYM and TSS questionnaires will be filled every 2 weeks during the study period. GES implantation together with the Heineke-Mikulicz PP will be performed laparoscopically (<10% of cases may require open approach). Only one surgeon using the same technique at all times will perform the surgeries. In GES-ON group, GES will be turned on immediately after the operation. On the other hand, in GES-OFF group, the GES will remain OFF for the first 3 months, while symptoms will be recorded again in both groups. After 3 months, follow up GET will be performed and in GES-OFF group, the device will be turned ON. Both groups will be followed for 3 more months clinically, to record any possible changes in their symptoms. Moreover, 36-Item Short Form Health Survey (SF-36), Beck depression inventory (BDI), State-trait anxiety inventory (STAI) and the patient health questionnaire (PHQ-15) will be completed at baseline followed by 3 and 6 months after the surgery. The amount of anti-emetics and prokinetics, days of hospitalization and ED visits and any possible complication will be recorded during the study period. Glucose control in diabetic patients will be monitored by HbA1c. Pain will also be monitored regarding narcotic need. During the follow-up patients will be instructed to remain on a mechanical soft diet of smaller meals, low fat, and low fiber. Evaluators of clinical outcome, the radiologist and the biostatistics consultant as well as the patient will remain blind to the GES-ON or -OFF status before the results get finalized. The individual programming the device will have no clinical rule to avoid any bias.

One of our Investigators, [name] is assigned to serve as an un-blind person, who is going to generate a master list of participants by dividing them into two groups based on their etiologies (diabetic or idiopathic). All efforts would be to include similar numbers of idiopathic and diabetic patients in each intervention group based on a block randomization method, allowing for GES to be turned ON at the surgery, or it will stay OFF for the 3-month-long blind portion of the study.

The following flow-diagram summarizes the steps of this study:

[figure not shown]

Early termination of the study will occur if a patient decides not to continue the study or if in the GES-OFF group, the nausea/vomiting symptoms are not manageable after 6 weeks of the operation, which is the usual time for surgical healing.

**Histological evaluation of the biopsy samples:** Paraffin embedded formalin fixed tissues will be cut at 3-4 microns thick and mounted on slides containing paired sections from cases and controls. Subsequently, the tissues will be deparaffinized and immunostained by BenchMark XT automated staining instrument. Briefly, the slides will through peroxidase block and antigen retrieval solutions before applying the primary antibodies (C-Kit clone YR145 from Cellmark, Rocklin, CA). Then, the slides will be washed and incubated with the secondary antibody followed by horseradish peroxidase (HPR). At the end, Chromogen will be added and the slides will be counter-stained by Hematoxylin. Pathology slides will be read by a pathologist who will be blind to the diagnosis of the patients, ICC will be counted per high power field (HPF) and the mean of ICC from examining 20 HPF will be calculated. For collagen fibrosis, the biopsies will be stained with trichome. Presence of diffusely distributed collagen between single muscle fibers will be defined as fibrosis and graded as mild, moderate and severe.

**Gastric emptying test:** Gastric emptying test will be performed utilizing a standardized meal consisting of egg beaters labeled with 99m technetium sulfur colloid accompanied by 2 toasts with strawberry jelly and 120 cc of water will be given to the patients (total calories- 240 and 2% fat). Anterior and posterior images will be obtained in the standing position immediately after meal ingestion and at 30 minutes, 1, 2, 3 and 4 hours. Geometric mean calculation and decay correction will be performed on all images. The radiologist will also be blind to the treatment groups.

The radiation exposure of a gastric emptying is equivalent to a chest x-ray or flying across country on an airline. Therefore, this test can be justified for repeating in 3 months.

**D4) Statistical analysis:** In the current study, the following parameters will be analyzed:

- 1) Changes of total gastroparesis symptom scores (TSS) and gastric retention of the radiolabeled meal (%) at 2-4 hrs in each group. TSS will include both severity and frequency.
- 2) Total Symptom Score (TSS) with severity and frequency of gastroparesis symptoms in each etiological subgroup of patients if enough study power would be achieved.
- 3) Associations between changes in gastric emptying and TSS.
- 4) Associations between changes in gastric emptying and ICC count/ pyloric fibrosis.

- 5) Associations between changes in TSS and ICC count/pyloric fibrosis.
- 6) SF-36, BDI, STAI and PHQ-15 scores and HBA1c (in diabetics) and their association with the treatment as well as gastric emptying/pathological findings.

The normal distribution of the data will be tested based on D'Agostino-Pearson omnibus test, were normality indicates parametric tests. The numerical variables will be reported as means (SD) or Median (Range) at baseline and follow-up visits and will be compared either by appropriate parametric or nan- parametric tests including t-test analysis or Mann–Whitney U test. The time-trends will be analyzed by either Repeated-Measure ANOVA or non-parametric Friedman Test followed by appropriate Post Hoc. Associations will be assessed based on Pearson correlation or Spearman's rho analysis. Data will be presented as bar graphs, time-trend graphs or scatter-plots and tables.

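### D2 rests a general non-inferiority claim for pyloroplasty alone on gastric emptying, an outcome the protocol says GES barely changes, while symptoms have no non-inferiority margin

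*Protocol*

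**What the plan says.** Section D2 gives the purpose in general terms: "this study is designed to conclude that pyloroplasty is not inferior to GES plus pyloroplasty". The sample size is then calculated "by including % normalization of the GE as the binary outcome". Its inputs are:

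- **Control rate:** "GE was normalized in 60 % of GP patients with GES-ON" plus pyloroplasty.
- **GES alone:** "GES alone normalizes GE in around 18% of GP patients, predominantly in idiopathic GP".
- **Margin:** "By defining non-inferiority limit equal to" 60 − 18 = 42 percentage points.
- **Size:** "17 patients will be included in each arm of this study", 34 in all. Alpha and power are not stated.

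Section D3 gives pyloroplasty to every patient. For the first 3 months the arms differ only in whether the stimulator is on.

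On what GES does, the Abstract says that "this therapy has minimal or no effect on the acceleration of gastric emptying (GE"), section B repeats this, and C2 concludes that "GES alone does not significantly accelerate gastric emptying". The benefit these sections claim for GES is on symptoms. Aim 1 concerns TSS and quality of life, Aim 2 gastric emptying, and Aim 3 both subjective and objective goals. D4 lists changes in TSS and in gastric retention first among its analyses, but names no primary outcome and no non-inferiority test.

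**The concern.** A non-inferiority comparison can show that a component is dispensable only on an outcome where that component is expected to work. Here the component being withheld is GES. The one outcome given a hypothesis, a margin and a size is one where the protocol expects GES to do little. Where GES is said to act, there is no margin and no sizing.

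The trial could therefore report in general terms that pyloroplasty is not inferior to the combination while patients with GES off have clearly worse nausea and vomiting. Aims 1 and 3 would appear to be answered when the non-inferiority test had not addressed their symptom part. The planned comparison of TSS does not close this gap, because failing to find a significant difference in 34 patients is not evidence of non-inferiority.

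**Working it through.** **1. Reproducing 17 per arm.** Take 60% in both arms, margin 0.42, one-sided 5% and 80% power. Alpha and power are inferred, because they return the protocol's figure.

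n = [0.6×0.4 + 0.6×0.4] × (1.645 + 0.842)² / 0.42² = 0.48 × 6.18 / 0.1764 = 16.8, so 17. One-sided 2.5% with 80% power would give 22.

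**2. What the margin rules out.** The null hypothesis is a loss of at least 42 points, which means normalization of 60 − 42 = 18% or less with GES off. The protocol credits GES alone with about 18 points. Even if all 18 were lost, the OFF arm would be at 60 − 18 = 42%, well inside the margin. The margin is 42/18 = 2.3 times that credit and 42/60 = 70% of the control success rate.

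**3. Chance of passing at 17 per arm, ON rate 60%.** Normal approximation: Φ[(0.42 − d)/SE − 1.645], where d is the true loss and SE = √{[p_ON(1−p_ON) + p_OFF(1−p_OFF)]/17}.

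- No GES effect (d = 0): SE = √(0.48/17) = 0.168, and Φ(2.50 − 1.645) = 80%.
- All 18 points lost (d = 0.18): SE = √(0.4836/17) = 0.169, and Φ(1.42 − 1.645) = 41%.

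| True OFF rate | Approximation, one-sided 5% | Exact binomial, 5% | Exact binomial, 2.5% |
|---|---|---|---|
| 60% | 80% | 81% | 71% |
| 50% | 60% | 61% | 47% |
| 42% | 41% | 42% | 29% |
| 18% | 5% | 4% | 2% |

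The true difference is almost sure to lie inside the margin, but a pass is not assured. None of these probabilities depends on symptoms.

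**4. Emptying and symptoms come apart in the protocol's own series.** In Table 2 (GES alone), the sum of the six D3 symptoms falls from 3.5+3+2.9+2.8+2.8+2.5 = 17.5 to 1.6+1.4+1.5+1.4+1.4+1.3 = 8.6. C2 reports that mean emptying did not change significantly.

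**5. What 34 patients deliver on TSS.** The documents give no SD for the sum, so it is assumed from the Table 1 post-operative item SDs (1.1, 1.0, 1.0, 1.2, 1.1, 1.5):

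- Inter-item correlation 0: √8.11 = 2.85.
- Inter-item correlation 1: sum of the SDs = 6.90.

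Margin for 80% power at one-sided 5%, with no true difference: 2.487 × SD × √(2/17).

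- SD 2.85: 2.4 points.
- SD 6.90: 5.9 points.

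For scale, the Table 1 post-operative sum is 1.1+0.6+0.9+0.9+1.0+1.0 = 5.5, so these margins are 44% to 107% of it. The uncontrolled post-operative gap between Tables 2 and 1 is 8.6 − 5.5 = 3.1 points. A margin of that size needs n = 2 × SD² × 6.18 / 3.1², or 11 to 62 per arm.

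**6. Two criteria together.** If each has 80% power and they are independent, joint power is 0.8 × 0.8 = 64%.

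**The case against.** The case for the plan has real weight.

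- **Emptying is a legitimate objective.** It is Aim 2 and part of Aim 3. This stands: the objection is to the breadth of the claim, not to measuring emptying.
- **Symptoms are compared.** TSS is recorded every 2 weeks in both blinded arms and heads the D4 list. A reader might infer that the trial says nothing about whether GES is needed for symptoms. That is true only of the GE non-inferiority result.
- **The test is not a formality.** A reader might infer that it can hardly fail. It fails about 19% of the time with no GES effect and about 58% of the time if 18 points are lost (exact, one-sided 5%). Only the position of the true difference is close to settled in advance.
- **D2 sizes the trial and D4 names no deciding test.** The role of GE is therefore read from D2 alone, and an SAP might add a rule. But D2 itself ties the general claim to GE, with outcome, margin and size.
- **The evidence on GES and emptying comes from GES without pyloroplasty.** The protocol has no data on pyloroplasty alone, so it does not prove that GES adds nothing once the pylorus is opened. This stands as a caveat on how alike the arms will be.

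**Conclusion.** The concern holds in a limited form. A pass on GE normalization cannot support the general statement in D2 or the symptom part of Aims 1 and 3, because the arms differ only in a treatment that the protocol says hardly affects emptying. On its figures, the 42-point margin exceeds by 2.3 times everything credited to GES alone. This rests on GES adding no more to emptying after pyloroplasty than it does alone. The pass probabilities rest on the inferred one-sided 5%.

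Two further inferences are not supported. One is that TSS would be far better powered at the same size: the SD is assumed, the 12.5-point fall in Table 1 (18.0 to 5.5) is an uncontrolled effect of both procedures, and 34 patients may support only a wide margin. The other is that a GE pass would show that GES status leaves emptying unchanged. A 42-point margin cannot show that.

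**What to change.** In D2:

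1. Limit the GE conclusion to this: GES-off was not worse than GES-on by more than the stated margin on GE normalization.
2. Make no general claim of non-inferiority unless 3-month TSS also meets a pre-stated, justified margin, as primary or co-primary outcome. Use the six-item severity sum defined in D3, and reconcile it with D4, where TSS includes both severity and frequency.
3. State what 34 patients deliver for that margin, with the assumed SD, alpha and power.

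The first change is wording only. The second needs no new measurement but has costs. The TSS margin must be justified, and joint power falls to about 64% on the assumptions above, so 34 patients may not be enough. D3 and Amendment 2 (item 8) let the blind phase end early when symptoms are not controlled, so the TSS analysis must say how those patients are handled. Otherwise their later scores could hide a loss with GES off. If these costs are not acceptable, the first change alone is sufficient, provided the general claim is dropped.

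### The 42-point non-inferiority margin in D2 is the gain from adding pyloroplasty, while the trial tests the loss from switching GES off, so meeting it would not show that pyloroplasty alone is close to the combination

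*Protocol*

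**What the plan says.** Protocol D2 (Sample Size) states the aim: "this study is designed to conclude that pyloroplasty is not inferior to GES plus pyloroplasty". The sizing outcome is normalisation of gastric emptying, "by including % normalization of the GE as the binary outcome". Two rates are used:

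- For the combination, "GE was normalized in 60 % of GP patients with GES-ON" plus pyloroplasty, taken from the preliminary data (C1 describes a 27-patient pilot).
- For the stimulator without pyloroplasty, from the site's database: "GES alone normalizes GE in around 18% of GP patients, predominantly in idiopathic GP".

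The margin is their difference, introduced with "By defining non-inferiority limit equal to" and worked out as 60 − 18 = 42%. From this margin and the success rate in the combination arm, D2 concludes that "17 patients will be included in each arm of this study", 34 in all. It cites the Blackwelder method but states no alpha, sidedness or power.

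D3 (Study Design) describes the comparison. Every patient receives the stimulator and a pyloroplasty. One group has the device turned on after surgery; in the other it stays off for the first 3 months, after which the follow-up emptying test is done. The Abstract and section B say that GES by itself does little or nothing to speed emptying.

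**The concern.** A non-inferiority margin has to be a tolerable loss in the thing being taken away. Here that is stimulation, since pyloroplasty is common to both arms. The 42 points compare patients with and without pyloroplasty, all of them stimulated, so they describe the other component. The protocol gives no figure for what GES adds on top of pyloroplasty and no clinical argument for accepting a 42-point loss.

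This is the only hypothesis for which the trial is sized. Section B asks whether pyloroplasty alone would do about as well as the combination. If a 42-point limit supports the answer, a reader could take a non-inferiority statement to mean near-equality on emptying when a very large loss is still compatible with the data.

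**Working it through.** **Inputs.** Reference rate 60%, GES-alone rate about 18%, margin 42 points, 17 per arm (all D2). Assumed because not stated: one-sided alpha of 5% or 2.5%, power of 80%, equal true rates of 60% in both arms, no losses to follow-up.

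**1. The plan's own figure.** n per arm = (z₁₋α + z₁₋β)² × [p(1−p) + p(1−p)] / margin².

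- One-sided 5%, 80% power: (1.645 + 0.842)² × 0.48 / 0.42² = 16.8, so 17. This matches D2.
- One-sided 2.5%, 80% power: 21.4, so 22.

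The arithmetic in D2 is therefore sound at one-sided 5% and 80% power.

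**2. What the margin tolerates.** With a true GES-ON rate of 60%, the null boundary for GES-OFF is 60 − 42 = 18%. As a share of the reference response, the loss is 42/60 = 70%.

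**3. Chance of declaring non-inferiority.** For x₁ of 17 successes with GES ON and x₂ of 17 with GES OFF, non-inferiority is declared if

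p̂₁ − p̂₂ + z₁₋α × √[p̂₁(1−p̂₁)/17 + p̂₂(1−p̂₂)/17] < 0.42.

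Summing the binomial probabilities of all passing pairs, with a true GES-ON rate of 60%:

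| True GES-OFF rate | One-sided 5% | One-sided 2.5% |
|---|---|---|
| 60% | 81% | 71% |
| 50% | 61% | 47% |
| 40% | 37% | 25% |
| 30% | 17% | 10% |
| 18% | 4% | 2% |

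**4. Example.** Take 10/17 (58.8%) ON and 8/17 (47.1%) OFF, an observed loss of 11.8 points. The upper bound on the loss is 39.7 points at one-sided 5%, which passes, and 45.1 points at one-sided 2.5%, which fails. With 7/17 OFF the bound is 45.4 points at one-sided 5%, which also fails.

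**5. What 34 patients can exclude.** The standard error at equal rates of 60% is √(0.48/17) = 0.168.

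- Power to exclude a 42-point loss: Φ(0.42/0.168 − 1.645) = 80% at one-sided 5%, and Φ(0.42/0.168 − 1.960) = 71% at one-sided 2.5%.
- Loss excluded if both observed rates are near 60%: 1.645 × 0.168 = 27.6, about 28 points; at one-sided 2.5%, 1.960 × 0.168 = 32.9, about 33 points.

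**6. Tighter margins at this size (illustration only).** With both true rates 60%, the same approximation gives power of 32% for 20 points, 23% for 15 and 15% for 10 at one-sided 5% (22%, 14% and 9% at one-sided 2.5%).

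**The case against.** Several points on the other side have weight.

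- **The decision rule is stricter than the margin suggests.** A reader might infer that any GES-OFF rate just above 18% would pass, or that a pass shows only that pyloroplasty alone beats GES alone. The documents do not support either. The test bounds the difference between the two arms; it does not compare GES-OFF with 18%. The two coincide only if the true GES-ON rate is 60%. Because the interval is wide, 10/17 ON needs at least 8/17 OFF to pass at one-sided 5%, and a true GES-OFF rate of 18% passes only about 4% of the time. This stands and limits the point.
- **The figures depend on an alpha recovered from the sample size.** True, so both levels are shown. At one-sided 2.5% the probabilities fall by 7 to 14 points at true rates of 50% to 30%, and 8/17 versus 10/17 no longer passes.
- **D4 lists no non-inferiority test.** The margin appears only in D2, and an analysis plan not shown may add to it. But D2 states the intended conclusion and derives the sample size from this margin, so the defect lies in what the protocol states and is not an omission.
- **Large losses are unlikely on the protocol's own view**, since it holds that GES hardly affects emptying. That makes the low-rate scenarios less likely. It does not justify the margin: if GES adds little to emptying, a 42-point allowance for removing it is harder to defend.

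Two further inferences are tempting and are not made. One is that the margin is a stated multiple of the GES effect; that would need the 18% to add to the pyloroplasty effect, which the protocol does not say. The other is a numerical lower confidence limit for the 42 points; that would need the size of the database behind the 18%, which D2 does not give.

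**Conclusion.** The concern holds. The margin is computed correctly as a subtraction, and 17 per arm follows from it at one-sided 5% and 80% power, but it is the increment from pyloroplasty in a trial that randomises GES. With a true GES-ON rate of 60% it excludes only GES-OFF rates at or below 18%, so meeting it would not establish that pyloroplasty alone performs much like the combination. A true rate of 40%, a 20-point loss, would be declared non-inferior in 37% of trials at one-sided 5% and 25% at one-sided 2.5%.

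These figures assume a Wald test, 17 evaluable patients per arm and a true GES-ON rate of 60%. The mismatch between the margin and the randomised contrast depends on none of these assumptions. It should be corrected before a non-inferiority conclusion is drawn from D2.

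**What to change.** In D2:

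1. Withdraw 42 points as a margin that supports a non-inferiority conclusion.
2. State what 34 patients can do: exclude a loss of about 42 points with 80% power at one-sided 5% (about 71% at one-sided 2.5%), and exclude about 28 points (33 at one-sided 2.5%) if both observed rates are near 60%. Name the alpha and power used.
3. Report the GES-OFF minus GES-ON difference in normalisation with its confidence interval as an estimate, without a non-inferiority claim.
4. Do not substitute 21 points: it is half of the same wrong-component difference and has no basis in the protocol. Any margin that is kept must be justified by the contribution of GES or by a clinically acceptable loss, with its power at 17 per arm stated.

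Cost: a change of protocol wording and a weaker stated claim. No extra patients and no change to procedures.
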